## Abstract

**Background:**

Fractures of the humeral shaft are associated with a profound temporary (and in the elderly sometimes even permanent) impairment of independence and quality of life. These fractures can be treated operatively or non-operatively, but the optimal tailored treatment is an unresolved problem. As no high-quality comparative randomized or observational studies are available, a recent Cochrane review concluded there is no evidence of sufficient scientific quality available to inform the decision to operate or not. Since randomized controlled trials for this injury have shown feasibility issues, this study is designed to provide the best achievable evidence to answer this unresolved problem. The primary aim of this study is to evaluate functional recovery after operative versus non-operative treatment in adult patients who sustained a humeral shaft fracture. Secondary aims include the effect of treatment on pain, complications, generic health-related quality of life, time to resumption of activities of daily living and work, and cost-effectiveness. The main hypothesis is that operative treatment will result in faster recovery.

**Methods/design:**

The design of the study will be a multicenter prospective observational study of 400 patients who have sustained a humeral shaft fracture, AO type 12A or 12B. Treatment decision (*i.e.*, operative or non-operative) will be left to the discretion of the treating surgeon. Critical elements of treatment will be registered and outcome will be monitored at regular intervals over the subsequent 12 months. The primary outcome measure is the Disabilities of the Arm, Shoulder, and Hand score. Secondary outcome measures are the Constant score, pain level at both sides, range of motion of the elbow and shoulder joint at both sides, radiographic healing, rate of complications and (secondary) interventions, health-related quality of life (Short-Form 36 and EuroQol-5D), time to resumption of ADL/work, and cost-effectiveness. Data will be analyzed using univariate and multivariable analyses (including mixed effects regression analysis). The cost-effectiveness analysis will be performed from a societal perspective.

**Discussion:**

Successful completion of this trial will provide evidence on the effectiveness of operative versus non-operative treatment of patients with a humeral shaft fracture.

**Trial registration:**

The trial is registered at the Netherlands Trial Register (NTR3617).

## Background

Humeral shaft fractures are associated with a profound temporary (in elderly sometimes even permanent) impairment of independence and quality of life. Fractures of the humeral shaft account for 1-3% of all fractures [1]. The cumulative incidence shows a peak in the working population (14.5/100,000 person years) as well as in the elderly (60/100,000) [1-3].

Humeral shaft fractures can be treated operatively or non-operatively. Operative treatment is mostly performed by intramedullary nailing, plate osteosynthesis, or external fixation. Non-operative immobilization is mostly done with a functional (Sarmiento) brace [4]. Operative and non-operative treatment strategies both have their pros and cons. Operative fracture fixation allows for early mobilization, which may lead to earlier functional recovery and reduced pain. However, surgical complications and fixation failure may occur [5]. Non-operative treatment may be associated with more pain (as the fracture is not stabilized) and discomfort (due to pain and immobilization) in the first weeks and may be associated with a higher malunion risk due to the lack of fracture re-alignment [6,7]. Longer immobilization may delay functional recovery.

Complications of operative and non-operative treatment overlap and data are lacking to determine treatment relatedness. Non-union occurs in 15-30% after operative treatment [5] versus 2-23% after non-operative treatment (for which most patients require secondary surgical treatment) [6,7]. The most feared disabling complication is radial nerve palsy, occurring in 2-17% of all patients [8-10]. A systematic review (n = 4,517 patients) reported an average radial nerve palsy of 11.8%. Although 70% recover spontaneously, the palsy was permanent in 12% of cases accounting for a substantial impairment and costs [9].

Regaining function is extremely important from a patient and societal perspective. From the few retrospective and prospective case series published, each using other outcomes, better functional outcome is expected after operative treatment [8,11-17].

The best type of treatment is still debated. Surgeons state that their experience, patient characteristics and expected physical demands in daily living guides treatment decision. In the elderly patients, some surgeons might prefer immobilization while others may primarily operate as they fear inferior functional outcome after non-operative treatment. In younger patients, some surgeons directly perform a surgical intervention while others primarily choose non-operative immobilization, followed by surgical intervention if needed. However, our retrospective study showed an approximately 50% operation rate irrespective of fracture subclass with no obvious differences in patient or fracture characteristics across classes [18]. Since randomized or high-quality comparative observational studies are lacking, a recent Cochrane review concluded there is no evidence of sufficient scientific quality available to inform the decision to operate or not [19]. High-quality clinical studies are thus urgently needed to resolve this clinically relevant problem. RCTs for this injury have shown feasibility issues; one RCT continued as an observational study due to severe recruitment problems [20]. The HUMMER study is designed to provide the best achievable evidence to answer this unresolved problem using an observational trial design.

The primary objective of this study is to examine the effect of operative versus non-operative treatment on the DASH (Disabilities of the Arm, Shoulder, and Hand) score, reflecting functional outcome and pain of the upper extremity, in adult patients who sustained a humeral shaft fracture. Secondary aims are to examine the effect of operative versus non-operative treatment on functional outcome, the level of pain, range of motion of the shoulder and elbow joint, the rate of secondary interventions and complications, the time to resumption of work and activities of daily living, health-related quality of life, costs, and cost-effectiveness in these patients.

## Methods/design

### Study design

The HUMMER trial will follow a multicenter, prospective observational trial design. Approximately 30 hospitals in The Netherlands will participate.

The decision to provide operative or non-operative treatment will be left to the discretion of the attending physician. We chose an observational design because a randomized controlled trial (RCT) would currently not be feasible. Many surgeons prefer not to participate in trials that involve randomization [21] and we know from experience that patients easily refuse to be randomized between operative and non-operative treatment. Inclusion problems were the main reason for failure of a previous RCT with the same research question as this study [20]. Well-designed and adequately reported observational studies are good alternatives to RCTs [22,23]. Preference of observational studies over RCTs in orthopedic trauma has been acknowledged [24,25]. They lead to similar outcomes without the limitations of randomization which may in practice decrease the validity of the outcomes [26,27]. These designs are increasingly used and accepted in surgical studies [28]. In order to answer our research question, we will make adjustments in the statistical analysis by using the propensity matching score method [29-32].

The trial is registered at the Netherlands Trial Register (NTR3617).

### Recruitment and consent

Eligible persons presenting to the ED with a humeral shaft fracture will be informed about the trial at the ED. After an explanation of the study, they will receive information and a consent form from the attending physician, the clinical investigator, or a research assistant. Patients meeting all inclusion criteria and none of the exclusion criteria will be included while they are still at the ED or at the time of their first outpatient visit.

As with many surgical trials, patients and surgeons cannot be blinded for treatment. In order to reduce bias, a research physician or research assistant will perform the follow-up measurements using a standardized protocol. Radiographs can also not be blinded for treatment; however, evaluating radiographs in duplicate by two trauma surgeons independently will improve reliability of fracture healing assessment. In case of disagreement they will discuss the results until they reach consensus. Finally, the analysis will be performed by a statistician without knowledge of treatment.

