### Study population

All persons aged 18 years or older presenting to the ED with a humeral shaft fracture (AO type 12A or 12B) are eligible for inclusion [33]. The AO type 12C fractures will be excluded due to their low occurrence rate. Humeral shaft fractures are defined as fractures located in the area between the surgical neck and the area immediately above the supracondylar ridge.

Patients meeting the following inclusion criteria are eligible for enrolment:

1. Adult men or women aged 18 years or older (with no upper age limit)

2. A fracture of the humeral shaft, AO class 12A or 12B (confirmed on X-ray)

3. Operation within 14 days after presentation to the ED (if this is the treatment of choice)

4. Provision of informed consent by patient

If any of the following criteria applies, patients will be excluded:

1. Patients with concomitant injuries affecting treatment and rehabilitation of the affected arm

2. Patients with a humeral fracture treated with an external fixator

3. Patients with a pathological, recurrent or open humeral shaft fracture

4. Patients with neurovascular injuries requiring immediate surgery (excl. radial nerve palsy)

5. Additional traumatic injuries of the affected arm that influence upper extremity function

6. Patients with an impaired upper extremity function (*i.e.*, stiff or painful arm or neurological disorder of the upper limb) prior to the injury

7. Retained hardware around the affected humerus

8. Patients with rheumatoid arthritis

9. Bone disorder which may impair bone healing (excluding osteoporosis)

10. Patients incapable of ensuring follow-up (*e.g.*, no fixed address or cognitive impairment)

11. Insufficient comprehension of the Dutch language to understand the rehabilitation program and other treatment information, as judged by the treating physician of researcher

Exclusion of a patient because of enrolment in another ongoing drug or surgical intervention trial will be left to the discretion of the attending surgeon on a case-by-case basis.

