### Intervention

The decision on treatment will be left to the discretion of the attending surgeon. The choice will be between operative and non-operative treatment. Also, the rehabilitation after treatment will not be standardized, but will be provided as in real life. Although this may create some heterogeneity across groups, it will improve the generalizability of the study results.

If a surgeon decides to operate the patient, the choice between plate osteosynthesis or intramedullary nailing will be left to the treating surgeon. No restrictions will be applied to the approach for reduction and fixation of the fracture, *e.g.*, open or closed, antegrade or retrograde. The type and brand of the materials as well as the use of cerclage wires and other elements of the surgery will be left to the surgeon, local availability and expertise. Critical elements of the operative treatment will be recorded (*e.g.*, type of implant, identification of the radial nerve, surgical approach, operative delay, duration of surgery) and the effect on outcome will be assessed.

In order to maximize generalizability, the type of non-operative treatment will also be left to the attending surgeon. Usually it consists of a splint, plaster, collar and cuff or hanging cast for 1–2 weeks, followed by a Sarmiento brace for 4–6 weeks. Critical elements of this treatment will be recorded and the effect on outcome will be assessed.

Due to a lack of evidence favoring a particular approach, the physical therapy and rehabilitation program will be recorded but not standardized. This will improve generalization of the study results.

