### Study procedures

Clinical evaluation will occur at two weeks (7–21 days window), six weeks (4–8 weeks window), three months (11–15 weeks window), six months (6–7 months window), and 12 months (12–14 months window) after start of treatment [Table 1]. These visits are standard of care for the targeted patient group. At each follow-up visit, the research coordinator or research assistant will ascertain patient status (*i.e.*, adverse events/complications, secondary interventions, etcetera, and will verify information within medical records).

**Table 1 T1:** Schedule of events

**Radiographs & events**	**Screening**	**Enrolment**	**Baseline**	**Post**	**2 weeks**	**6 weeks**	**3 months**	**6 months**	**12 months**
				**surgery**	**(7–21 d)**	**(4–8 we)**	**(11–15 we)**	**(6–7 mo)**	**12-14 mo)**
X-ray	X						X^1^	X^1^	X^1^
Screening	X								
Informed consent		X							
Baseline data			X						
Surgical report form				X					
DASH					X	X	X	X	X
Pain (VAS)					X	X	X	X	X
SF-36					X	X	X	X	X
EQ-5D					X	X	X	X	X
Clinic FU					X	X	X	X	X
Range of motion					X	X	X	X	X
Secondary interventions					X	X	X	X	X
Complications					X	X	X	X	X
Health care consumption					X	X	X	X	X
ADL/work resumption					X	X	X	X	X
Physical therapy					X	X	X	X	X
Constant score						X	X	X	X
Early withdrawal					*	*	*	*	*

^1^X-rays will be taken according to local protocol; all X-rays after three months will be analyzed. The six-month X-ray is needed for assessing fracture healing. If no signs of healing are seen at six months, the 12-month X-ray is also required.

*Only at time of withdrawal.

At each follow-up visit, the range of motion of the shoulder and elbow will be measured using a goniometer by a physician or research assistant. In addition, patients will be asked to complete the questionnaires relating to disability (DASH score including optional modules), pain (VAS), health-related quality of life (SF-36, EQ-5D), health care consumption and production loss. From six weeks onwards, the research coordinator or research assistant will determine the Constant score.

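### Inclusion may wait until the first outpatient visit and need not precede the operation, so some operated patients can enter, or decline, with their early surgical course known

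*Protocol article*

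**What the plan says.** Under Recruitment and consent, eligible persons "will be informed about the trial at the ED", and those who meet the criteria "will be included while they are still at the ED or at the time of their first outpatient visit". The limit is a type of visit. It is not a number of days and is not tied to the operation.

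Under Study population, consent is an inclusion criterion ("Provision of informed consent by patient"). Two other criteria depend on the treatment actually given. One inclusion criterion begins "Operation within 14 days after presentation to the ED (if this is the treatment of choice"), and one exclusion reads "Patients with a humeral fracture treated with an external fixator".

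Under Intervention, allocation is not random: "The decision on treatment will be left to the discretion of the attending surgeon".

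Under Study procedures, follow-up is counted from the start of treatment and the first visit falls at 7–21 days. Table 1 orders its columns as screening, enrolment, baseline, post surgery, then the follow-up visits. The row "Surgical report form" is marked in the post-surgery column, after enrolment and baseline.

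**The concern.** A visit-based limit can mean different things in the two groups. A non-operative patient sent home from the ED reaches the first outpatient visit with treatment still under way. A patient admitted from the ED and operated on during that stay has no outpatient visit until after discharge. For that patient the rule permits inclusion after surgery, when patient and surgeon may already know of an infection, a wound problem, a nerve palsy or an implant failure. The article lists all of these as complications to be compared between groups.

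If such knowledge affects who is approached or who consents, the operated group is selected in part on its own early outcome. The DASH, complication and secondary-intervention comparisons would all be exposed. In a non-randomised study the defence against bias is adjustment, and adjustment cannot bring back patients who never entered the data.

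**Working it through.** **Reading the text.**

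1. Does any sentence place inclusion or consent before the operation? No. Informing patients at the ED is required; including them there is one of two options.
2. Does Table 1 settle it? It shows an intended sequence through its column order, but no footnote or text makes that order a rule. It is inconsistent with what the recruitment sentence permits, without forbidding it.
3. Who can be affected? Operated patients whose first outpatient visit comes after the operation. The article does not say how many there are.
4. What could select them? Mainly consent. The ethics section mentions a waiver of consent, but the inclusion criteria still require consent, so it is treated here as needed. The two treatment-dependent criteria can be confirmed only once treatment has been given, which leaves room for late eligibility decisions.
5. Can the analysis repair it? The mixed model adds intrinsic and fracture-related covariates. The propensity model names fracture type, age, gender, mechanism of injury, dominance and activity levels. None of these describes the course of surgery. The bias controls listed under Recruitment and consent (standardised follow-up, duplicate radiograph reading, a statistician unaware of treatment) concern measurement and analysis, not entry.

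**Benchmark from the article.** The sample size section assumes DASH 16 (SD 16) non-operative and 10 (SD 10) operative, a difference of 6. With two-sided α 0.05 and 80% power, n = (16² + 10²)(1.960 + 0.842)² / 6² = 77.6, so 78 per group as stated; 78 × 1.1 × 1.1 = 94.4 gives the stated 95. The 6-point difference is therefore a sound yardstick.

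**Illustration; none of these inputs is in the document.** Let f be the share of operated patients with a poor early course, D their excess DASH, and m the share of them never included. The observed poor-course rate is f(1 − m)/(1 − fm). The operative mean is too low by D × [f − f(1 − m)/(1 − fm)].

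- Half of operated patients included after surgery, f = 10%, D = 20, and half of the poor-course patients in that late half missed: m = 0.5 × 0.5 = 0.25. Rate = 7.5/97.5 = 7.7% instead of 10%. Shift = 20 × (0.1000 − 0.0769) = 0.46 points, or 8% of 6.
- All operated patients included after surgery, other inputs the same: m = 0.5. Rate = 5/95 = 5.3%. Shift = 20 × (0.1000 − 0.0526) = 0.95 points, or 16% of 6.
- Wider range, with f 5–15%, D 10–20 and m 25–100%: shift 0.12 to 3.0 points, or 2% to 50% of 6. The upper end needs 15% poor courses, all of them missed.

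**The case against.** The best defence is that the sections, read together, describe identification at the ED and enrolment before surgery, with the first outpatient visit as a fallback for patients sent home. Open fractures and neurovascular injuries needing immediate surgery are excluded, which removes an obvious group going straight to theatre. Operation may follow days later, so an outpatient visit can come first. The exclusions mostly describe the injury or the state before it, and leaving a patient out for a poor postoperative course would breach them. The same sentence governs both groups, so non-operative patients can also be lost before a late inclusion. Finally, the illustrated shifts are modest: with 200 per group the standard error of the difference is √((16² + 10²)/200) = 1.33 points.

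Much of this stands. A reader might infer that Table 1 flatly contradicts the recruitment sentence, that only operated patients pass through a filter, or that operative results are thereby made to look better. The document supports none of these. The column order implies a sequence without imposing one, late entry is open to both groups, and the direction of any bias is not given.

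What the defence does not remove is the permission itself. Being informed at the ED is not being included there, and consent can still be refused later. Only operated patients can have completed the main intervention by the time they enter. A bias below one standard error is still a bias, and it does not shrink as recruitment grows.

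**Conclusion.** The concern holds as a selection risk that the written rule permits. The document does not show that such selection occurs, how many patients it could reach, or which way it would act. If operated patients with a poor course were the ones lost, the effect would favour surgery, which is the direction of the study's hypothesis. On the assumed inputs of the two main illustrations, the operative mean DASH would be about 0.5 to 0.9 points too low against a planned 6. The recorded poor-course rate would fall from 10% to between 7.7% and 5.3%, so complication comparisons could be affected relatively more than the mean DASH. These figures show scale only and are not estimates for this study. The change is worth making because it is cheap and the planned adjustment cannot do the same job.

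**What to change.** Reword the recruitment sentence so that it agrees with Table 1:

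- State that eligibility is judged from ED and injury data in both groups and is not re-judged after surgery.
- Set the same latest inclusion day, counted from ED presentation, for both groups.
- Record the inclusion date relative to the operation or the start of treatment.
- Flag patients included after surgery and repeat the primary analysis without them as a sensitivity analysis.

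A blanket bar on inclusion once treatment has started would not serve. Splinting at the ED may itself start non-operative treatment, so such a bar could exclude first-visit entrants in that group and create a new imbalance.

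The cost is one reworded passage, one date field, one extra analysis, and a few patients flagged or not included. The sensitivity analysis will not recover missed patients. It shows whether the result depends on those who entered after surgery.

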### Study population

All persons aged 18 years or older presenting to the ED with a humeral shaft fracture (AO type 12A or 12B) are eligible for inclusion [33]. The AO type 12C fractures will be excluded due to their low occurrence rate. Humeral shaft fractures are defined as fractures located in the area between the surgical neck and the area immediately above the supracondylar ridge.

Patients meeting the following inclusion criteria are eligible for enrolment:

1. Adult men or women aged 18 years or older (with no upper age limit)

2. A fracture of the humeral shaft, AO class 12A or 12B (confirmed on X-ray)

3. Operation within 14 days after presentation to the ED (if this is the treatment of choice)

4. Provision of informed consent by patient

If any of the following criteria applies, patients will be excluded:

1. Patients with concomitant injuries affecting treatment and rehabilitation of the affected arm

2. Patients with a humeral fracture treated with an external fixator

3. Patients with a pathological, recurrent or open humeral shaft fracture

4. Patients with neurovascular injuries requiring immediate surgery (excl. radial nerve palsy)

5. Additional traumatic injuries of the affected arm that influence upper extremity function

6. Patients with an impaired upper extremity function (*i.e.*, stiff or painful arm or neurological disorder of the upper limb) prior to the injury

7. Retained hardware around the affected humerus

8. Patients with rheumatoid arthritis

9. Bone disorder which may impair bone healing (excluding osteoporosis)

10. Patients incapable of ensuring follow-up (*e.g.*, no fixed address or cognitive impairment)

11. Insufficient comprehension of the Dutch language to understand the rehabilitation program and other treatment information, as judged by the treating physician of researcher

Exclusion of a patient because of enrolment in another ongoing drug or surgical intervention trial will be left to the discretion of the attending surgeon on a case-by-case basis.

